#### KPI and interrupted time series analysis

Interrupted time series (ITS) analyses will be done using autoregressive integrated moving average (ARIMA) models to account for temporal trends and to determine whether there were changes in the process and clinical outcomes at the intervention period (compared with the baseline period) associated with implementation of the evidence-based acute KRT pathway. Each KPI will be assessed separately, as well as in aggregate with other KPIs. Autocorrelation, partial autocorrelation, and inverse autocorrelation functions will be assessed for model parameter appropriateness and seasonality. Stationarity will be assessed using the autocorrelation function and the augmented Dickey–Fuller test. The presence of ‘white noise’ was assessed by examining the autocorrelations at various lags, using the Ljung–Box χ2 statistic.

#### Healthcare system costs analysis

The primary health economic evaluation will be a within-study analysis of the cost-effectiveness of the Dialyzing Wisely program. Subject to available resources we will consider additional model-based analyses of Dialyzing Wisely over a longer time horizon.

The within-study analysis will be conducted on resource use and outcomes occurring during the study period. It will include total quarterly acute KRT-associated costs for each specific ICU following the implementation of KPI reporting. The cost analysis will include 1) utilization costs of CKRT filters, CKRT fluids, KRT anticoagulation (if any),and KRT catheters. Costs will be calculated in part using acute KRT process measures captured by our acute KRT KPIs.

We will also conduct an analysis of healthcare systems costs including those associated with total ICU and hospital stay and ongoing new ESKD costs (i.e., long-term, maintenance dialysis costs, total healthcare costs. Healthcare system costs will be reported as costs of acute KRT in ICU as a proportion of total ICU costs per quarter. Modeling analysis will capture costs to the health service, social care providers and patients so as to provide cost estimates from a societal perspective. We will determine models for averted and delayed acute KRT and averted new end-stage kidney disease requiring chronic dialysis based on observed changes in practice based on prescriber reports and adherence to best-evidence. Results will be reported as the incremental net benefit and incremental cost-effectiveness ratios. Uncertainty will be captured in the analyses through probabilistic sensitivity analysis and reported using cost- effectiveness acceptability curves, showing the likelihood the intervention will be cost-effective over a range of values of willingness-to-pay thresholds for specific outcomes.

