### Trial oversight

Dialyzing Wisely will be governed by an Executive Committee. The Executive Committee will be comprised of Leads from 4 participating Strategic Clinical Networks (SCNs) (Critical Care, Medicine (Kidney Health Section), Cardiovascular Health and Stroke, and Maternal, Newborn, Child and Youth). SCNs are province-wide integrated teams that collaboratively identify and solve challenges within their specific area of health. SCN membership includes clinicians, patients, operational leaders, researchers, community and industry partners and other stakeholders [19].

The Executive Committee will be supported by an International Advisory Panel. This panel will be made up of critical care nephrology experts with a specific interest in quality and safety for acute KRT. The International Advisory Panel will provide a high-level review of program performance and will provide unbiased recommendations to ensure ongoing advancement and program success.

The program will also have a Steering Committee with representation from all stakeholder groups (i.e., physicians, nurses, educators, administrators, operational leads, epidemiologists, health economists, informatics specialists and patient-partners). This Steering Committee will review KPI reports and study developments to ensure ongoing appropriate program advancement and oversight.

Finally, key stakeholders have been identified at each individual study site to operationalize and champion the implementation of the acute KRT pathway and enact change. We will also include provincial organizations to facilitate our audit and feedback process and transition ownership of the program to local sites. This will include members listed above as well as the Alberta Medical Association Physician Learning Program (PLP).

All aspects of the governance will be overseen by the program manager, and facilitated by the research assistant. Key reporting and educational messaging will be delivered by Clinical Practice Leads with expertise in knowledge translation strategies (Fig. 4).

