### Data management

Effects of prescriber and acute KRT program patterns in the initiation of acute KRT will be determined by monitoring resource use associated with initiation of KRT at both a program level and healthcare system level. This will be done by determining first the units of each resource and then by assigning costs to each unit. At the program level we will capture the number of acute KRT initiations as well as total patient-days of acute KRT per specific modality (i.e., intermittent or continuous). These acute KRT initiations will also be adjusted for severity of illness to enable translation across units with varying case-mix, acuity and workload. Acute KRT disposable costs will include KRT filters, catheters, replacement and anticoagulation solutions.

New intake of critically ill survivors with severe AKI into ESKD dialysis programs will be reviewed on a quarterly and yearly basis to determine any changes relevant to use of this resource to the Alberta healthcare system. We will ensure that any changes in intakes reflect acute KRT initiations based on adherence to best-evidence practices.

Data will be collected on patient characteristics: (i.e., demographics, type of admission [medical, surgical, trauma]), clinical status (i.e., comorbid diseases including chronic kidney disease, primary diagnosis), acuity (i.e., APACHE II, SOFA, CFS), ICU treatment (i.e., duration of renal replacement therapy, mechanical ventilation, vasoactive therapy), ICU and hospital lengths of stay, and outcomes (i.e., renal recovery and mortality); and KRT-associated resource data: (i.e., filter use, prescription/dose, machine alarms/down time, anticoagulation, re-hospitalizations, progression of renal disease). Data variables to be captured are summarized in Table 4.

**Table 4 Tab4:** Data variables

Data Variable	Description
ICU location	admission ICU
Age	years
Sex:	M/F
Weight	kg
Date of Hospital Admission	dd/mm/yyyy
Date of ICU Admission (dd/mm/yyyy):	dd/mm/yyyy
Admission class	med/surg/neuro/trauma
ICU discharge location	unit/hospital
ICU Admission Diagnosis – cardiovascular, respiratory, gastrointestinal, genitourinary/renal, endocrinological/metabolic, neurological, trauma, burn, sepsis, surgery	yes/no
Co-morbidities – AIDS, chronic RRT, chronic heart failure, respiratory insufficiency, cirrhosis, diabetes mellitus, hepatic failure, immune suppression, leukemia, lymphoma, metastatic cancer, coronary artery disease	yes/no
Clinical Frailty Scale	number

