#### Health-related quality of life and patient-reported outcome measures

Cost-effectiveness will be analyzed by estimating incremental cost and effectiveness based on, patient life-years gained and quality-adjusted life years [QALY]) gained. These will also be modeled based on adherence to best evidence-based practices and anticipated outcomes. QALYs will be calculated based on health-related quality of life as measured by the EQ-5D-5L and the PedsQL in children.

PROMs analysis will be conducted by quality-of-life assessment using the ESAS-r and/or the IPOS-renal scales [22]. This data will be collected at first chronic dialysis session. Quantitative analysis will be done to assess changes in scores using a linear mixed effects model with the baseline score as a fixed effect co-variate, and dialysis unit, with each cluster as a random intercept.

All statistical analyses will be done using SAS Enterprise Guide 7.1 (Cary, NC), TreeAge Pro (TreeAge Software Inc., Williamstown MA) and Excel (Microsoft, Redmond VA).

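### The economic analysis can mislead: system cost is reported as a ratio without hospital or ESKD cost, the ICER is not tied to observed outcomes, and no cost list names delivery cost

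*Protocol article*

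**What the plan says.** Primary outcomes lists acute KRT and health-system costs. All quotations are from the protocol article.

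- **Type of evaluation** (Healthcare system costs analysis): "The primary health economic evaluation will be a within-study analysis of the cost-effectiveness of the Dialyzing Wisely program". It is to rest on what is consumed and observed while the study runs. Longer-horizon modelling is optional.
- **Period** (same section): "It will include total quarterly acute KRT-associated costs for each specific ICU following the implementation of KPI reporting".
- **Items costed** (same section): "utilization costs of CKRT filters, CKRT fluids, KRT anticoagulation (if any),and KRT catheters". Data management words this differently: "Acute KRT disposable costs will include KRT filters, catheters, replacement and anticoagulation solutions". Table 4 adds, among others, re-hospitalisation, chronic KRT and an undefined item for provider-related costs.
- **System costs** (same section): these include total ICU stay, hospital stay and new ESKD, but are to be reported as "costs of acute KRT in ICU as a proportion of total ICU costs per quarter".
- **Modelling** (same section): averted or delayed KRT and averted ESKD are to be modelled from observed practice change and adherence. The next sentence promises incremental net benefit and ICERs.
- **Effects** (Health-related quality of life section): after naming life-years and QALYs, the text says "These will also be modeled based on adherence to best evidence-based practices and anticipated outcomes".
- **Delivery resources** (Trial oversight): "All aspects of the governance will be overseen by the program manager, and facilitated by the research assistant". Clinical Practice Leads deliver the reporting and education, and Table 3 adds seminars, site visits, a website and weekly communications.

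**The concern.** An ICER needs the full cost of both alternatives and an effect whose source is clear. Three features put that at risk.

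1. The reporting measure for system costs leaves out two of the components that the same paragraph says system costs contain, and it moves with its denominator.
2. Adherence is what the prescriber reports try to change, and the number of appropriate initiations is itself a primary outcome. If adherence is then converted into averted dialysis and QALYs, better adherence produces benefit on paper even when observed deaths and dialysis dependence stay the same.
3. Running the pathway costs money on the intervention side only. Leaving that cost out lowers the incremental cost.

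At stake is whether a health system is told that the programme saves money or is worth its cost.

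**Working it through.** The protocol states no total cost, saving or ICER, so there is no figure to reproduce. The inputs below are from Acute KRT in Alberta (2019): 3278 continuous (CKRT) days at $764–865, 398 intermittent (IKRT) days at $528, 56 possible extra ESKD patients a year, and more than $100,000 per ESKD patient a year.

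**Direct acute KRT cost**
- CKRT: 3278 × $764 = $2,504,392; 3278 × $865 = $2,835,470.
- IKRT: 398 × $528 = $210,144.
- Total: $2,714,536 to $3,045,614. The IKRT share is 210,144 / 3,045,614 = 6.9% to 210,144 / 2,714,536 = 7.7%.

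**1. The ratio.** If KRT cost changes by a factor a and total ICU cost by a factor b, the ratio changes by a / b. It rises whenever ICU cost falls by the larger percentage. Illustration (assumed): KRT cost 5 out of ICU cost 100 is 5.0%. With KRT cost down 10% and ICU cost down 15%, 4.5 / 85 = 5.3%. Both costs fell, yet the reported measure rose.

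**2. Modelled ESKD benefit.** 56 × $100,000 = $5.6M a year. Against direct acute KRT cost: 5.6 / 3.046 = 1.8 and 5.6 / 2.715 = 2.1. Crediting 10%, 25% or 50% of these cases as averted gives $0.56M, $1.4M or $2.8M for one year of dialysis. A 10% fall in acute KRT cost is worth $271,454 to $304,561, the annual cost of about three ESKD patients. A small modelled number therefore outweighs a sizeable observed saving.

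**3. Delivery cost.** The protocol gives none, so both the 10% saving and the delivery costs are assumptions, and only acute KRT costs are counted.

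| Delivery cost a year | Net result at a 10% KRT saving |
|---|---|
| $100,000 | saving of $171,454 to $204,561 |
| $300,000 | from a net cost of $28,546 to a saving of $4,561 |
| $500,000 | net cost of $195,439 to $228,546 |

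Break-even equals the saving itself: $0.27–0.30M at 10%, $0.14–0.15M at 5%, and $0.54–0.61M at 20%.

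**Wording points.** The quarterly cost sentence names no baseline quarters. The cost section restricts filters and fluids to CKRT, where Data management lists KRT filters without restriction.

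**The case against.** The strongest reply is that the stated hierarchy is already sound. The within-study analysis is primary and uses observed outcomes, QALYs use measured EQ-5D-5L and PedsQL, and the sentence on modelling says *also*, which can be read as an addition. Probabilistic sensitivity analysis is planned. The ratio may be purely descriptive, since nothing says that it enters the ICER. The break-even sum sets delivery cost against acute KRT savings alone, although ICU, hospital and ESKD costs are in scope. The provider-related item in Table 4 may cover part of delivery, and an article condenses a fuller costing plan.

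Much of this stands, and it limits the point. A reader might infer three stronger claims that the document does not support:

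- *That the ICER favours the pathway by construction.* The ratio can just as well count against the pathway, and an unnamed baseline leaves the increment undefined, not favourable. Only the unnamed delivery cost and the adherence-driven benefit push one way.
- *That IKRT supplies are left out.* Anticoagulation and catheters are listed for KRT in general, Data management and Table 4 use modality-neutral items, and patient-days are captured for both modalities. What remains is a wording mismatch within a 6.9–7.7% cost share.
- *That costs are taken only after implementation.* The sentence says what the analysis includes. The Abstract and Statistical analyses compare with baseline, and incremental results imply a comparator.

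The reply does not settle which outcomes feed the reported ICER, because the promise of ICERs directly follows the adherence-driven models. Nor does it repair a system-cost measure that omits hospital and ESKD cost.

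**Conclusion.** The concern holds in this limited form. The ratio is a fault in what the protocol fixes: it cannot show the system costs that the protocol defines, and it can worsen when costs fall. The source of effect in the ICER is ambiguous, and on the protocol's own figures the modelled ESKD term is potentially 1.8 to 2.1 times all direct acute KRT cost. That comparison takes the 56 patients and $100,000 at face value. The protocol words the first as a possibility and the second as a lower bound.

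The unnamed delivery cost tends to lower incremental cost. Its size is unknown. Break-even near $0.3M a year rests on an assumed 10% saving and on acute KRT costs alone, and counting ICU, hospital or ESKD savings would raise it. The missing baseline quarters and the CKRT/KRT mismatch are minor wording points.

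**What to change.** - Report absolute system costs per KRT patient and per ICU admission, with hospital and ESKD costs included, in place of the ratio or ahead of it.
- State that the primary ICER and net benefit use observed deaths, observed dialysis status and measured utilities. Label adherence-driven modelling of KRT, ESKD, life-years and QALYs as a scenario.
- Add pathway delivery as a named cost item (programme staff, education, report building), taken from programme budget records, and define the provider-related item in Table 4 so that nothing is counted twice.
- Use one cost list for both modalities, and apply it to each ICU's baseline and intervention quarters.

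The cost is a wording change and a little more analysis. Mortality, 90-day KRT dependence and quarterly intake into chronic dialysis are already to be collected or reviewed. The result may be less favourable to the pathway.

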## Background

Acute kidney replacement therapy (KRT) is a core life support technology used in approximately 10–12% of critically ill patients [1]. It is generally used to support patients with overt kidney failure or as part of a broader strategy for multi-organ support in ICU settings, along with mechanical ventilation and vasoactive medications. Its utilization has expanded, with recent estimates showing growth of more than 10% per year [2, 3]. Acute KRT in the ICU can be delivered intermittently (i.e., intermittent kidney replacement therapy [IKRT]) or continuously (i.e., continuous kidney replacement therapy [CKRT]) depending on the available technology.

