### Research questions

Can we develop and implement a standardized framework to be implemented in all acute KRT programs?Will monitoring the performance of our acute KRT delivery by means of evidence-based KPIs result in improved performance and a decrease in acute KRT program costs?Can we rapidly implement the findings of novel programs of research into clinical practice to improve patient-centered outcomes and decrease both short and long-term healthcare costs?

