### Interventions, duration and frequency of follow-up

The acute KRT pathway will consist of two specific interventions:Monitoring, reporting and audit of acute KRT KPIs.Provision of individualized prescriber and program reports for acute KRT initiation patterns.

The acute KRT care pathway will be implemented in a stepwise fashion with a pilot followed by randomized stepped wedge roll out at centres across Alberta over the subsequent 21 months. Roll out of ICUs will be performed in clusters and will coincide with individual site activation of a novel, province-wide electronic provincial clinical information system (CIS), Connect Care (EPIC, Verona WI).

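### Acute KRT cost is stated as a quarterly total per ICU with no KRT-volume denominator, so a KPI-driven saving could be hidden or mimicked by changes in volume

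*Protocol article*

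**What the plan says.** All references are to the protocol article. Primary outcomes lists acute KRT and healthcare system costs without a unit of measurement. Research questions asks whether KPI monitoring will "result in improved performance and a decrease in acute KRT program costs".

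Healthcare system costs analysis then describes the within-study analysis: "It will include total quarterly acute KRT-associated costs for each specific ICU following the implementation of KPI reporting". The components are "utilization costs of CKRT filters, CKRT fluids, KRT anticoagulation (if any),and KRT catheters". One ratio follows: "Healthcare system costs will be reported as costs of acute KRT in ICU as a proportion of total ICU costs per quarter". Incremental net benefit and incremental cost-effectiveness ratios are also promised.

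KPI and interrupted time series analysis uses ARIMA models to allow for temporal trends. It names process and clinical outcomes, and each KPI, but not cost.

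Data management says that the number of initiations and "total patient-days of acute KRT per specific modality" will be captured for each program. It adjusts initiations for severity of illness, but states no such adjustment for cost. Table 4 adds site admissions and patient-days.

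**The concern.** The pathway has two parts that act on different terms of the cost. KPI feedback on filter life and downtime works mainly on what a day of KRT costs. Prescriber reports work on how many KRT days there are. Growth in use also works on the number of days, and the Background says of KRT: "Its utilization has expanded, with recent estimates showing growth of more than 10% per year". The listed components are consumables, which rise and fall with volume.

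A total combines these influences. If volume grows, a real saving per day can be reported as a rise in cost. If volume falls for an unrelated reason, the fall can be credited to KPI monitoring. Either misreading would bear on the research question about program costs.

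**Working it through.** The article states no cost effect, power or sample size, so there is no figure to reproduce. The check is direct arithmetic.

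**Inputs from the article**
- Growth in KRT use: 10% per year (Background, which says more than 10%).
- Period: 21 months (Interventions, duration and frequency of follow-up: "randomized stepped wedge roll out at centres across Alberta over the subsequent 21 months").
- 2019 volume and unit cost (Acute KRT in Alberta): 3278 continuous days at $764–865 and 398 intermittent days at $528.

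**Assumed inputs**
- Saving per KRT day *s* = 10%.
- Growth range 5% to 15% per year.
- Growth in total ICU cost 0% to 10% per year.

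**1. Scale.** 3278 × 764 + 398 × 528 = $2,714,536, and 3278 × 865 + 398 × 528 = $3,045,614. The base is therefore about $2.71–3.05 million per year. These are direct healthcare costs, which the article does not equate with the consumables listed for the cost analysis. The percentages below do not depend on this base.

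**2. Effect of growth on the total.** With growth *g* over *m* months, the volume factor is F = (1 + g)^(m/12). The change in the total is F(1 − s) − 1. The total falls only if *s* exceeds 1 − 1/F.

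| Growth per year | Months | F | Change in total, s = 10% | Break-even saving |
|---|---|---|---|---|
| 5% | 21 | 1.089 | −2.0% | 8.2% |
| 10% | 12 | 1.100 | −1.0% | 9.1% |
| 10% | 21 | 1.182 | +6.3% | 15.4% |
| 10% | 24 | 1.210 | +8.9% | 17.4% |
| 15% | 21 | 1.277 | +14.9% | 21.7% |

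Cost per KRT day shows −10% in every row.

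**3. The reverse case.** If KRT days fall by 10% for any reason and cost per day is unchanged, the total changes by 0.90 × 1.00 − 1 = −10%, while cost per day changes by 0%. So the total can mimic a KPI saving, and cost per day alone would miss averted KRT. Both are needed.

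**4. Share of total ICU cost.** With 10% KRT growth, a 10% saving per day and ICU cost growth *h*, the share at 21 months changes by 1.182 × 0.90 / (1 + h)^1.75 − 1. This gives +6.3%, +1.0%, −2.4% and −10.0% for *h* = 0%, 3%, 5% and 10%. The same saving can look like a rise or a fall, depending on ICU spending.

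**5. Trend adjustment.** A simulation used one series of 20 quarters (12 before, 8 after), 10% yearly growth and a 10% saving per day. Noise was 5% to 20% in quarterly volume and 3% in unit cost. All of this is assumed, and a log-linear segmented regression stood in for ARIMA.
- Raw pre-post total: about +14%.
- Trend-adjusted total: about −10%, with a standard deviation of the log estimate of 0.05 to 0.18.
- Cost per KRT day: −10%, with a standard deviation of 0.014. This precision follows from the assumed 3% noise.

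Trend adjustment recovers the saving when the trend is stable, but less precisely than cost per day does here.

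**The case against.** The strongest reply has five parts.

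- **The sentence is not exclusive.** It says what the analysis will include and does not define the sole cost outcome. This stands. But no other measure of acute KRT cost with a volume denominator is stated.
- **A total suits a question about program cost, and averted KRT is a target.** This stands, and is why the total should stay.
- **Volume and unit cost are recorded separately, so cost per KRT day can be computed.** This also stands. A reader might infer that the research question on cost cannot be answered. The planned data do not support that; the stated measure alone does not answer it cleanly.
- **The growth figure is a background estimate, and the arithmetic is an unadjusted start-to-end comparison.** This stands. A reader might infer that growth will hide a saving; the documents support only that it could. At 5% growth the assumed saving shows as a fall. Comparison with ICUs not yet activated in the same calendar period could absorb shared growth, but no such comparison is stated for cost, and it would not separate cost per day from number of days.
- **A condensed article may leave normalisation and the cost model to a fuller plan.** This is fair, and it limits the weight of the point. The point concerns the measure the article does state, not a missing detail.

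The stated total also refers only to quarters after KPI reporting starts. A reader might infer that no baseline cost comparison is planned. The Abstract's comparison with baseline and the incremental results in the cost section speak against that.

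**Conclusion.** The point holds as a weakness in the stated measure. Acute KRT cost per ICU-quarter has no KRT-volume denominator, the one ratio given does not supply it, and the trend model is not said to cover cost. Under continued growth of 10% per year, an assumed 10% saving per KRT day would show as about +6% in the unadjusted total at 21 months, and the break-even saving is about 15%. For assumed growth of 5% to 15% per year the break-even runs from 8% to 22%. These figures rest on the background growth applying to these ICUs and on no trend adjustment for cost. The documents do not support calling the total wrong in itself. This is a cheap improvement to the reporting of a primary outcome.

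**What to change.** In Healthcare system costs analysis:

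- Keep the total quarterly cost per ICU.
- Add acute KRT cost per KRT patient-day, by modality. This addresses KPI performance.
- Add acute KRT cost per ICU admission or per ICU patient-day. This addresses use of KRT.
- Report all three for baseline and intervention quarters.
- State that the model in KPI and interrupted time series analysis also applies to these cost measures.

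The denominators are already listed in Data management and Table 4, so no new data are needed. The price is a little more analysis and two more reported cost measures.
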